### 6.3 End-of-treatment visit

The End-of-Treatment assessments should be performed no later than 14 days after study treatment has stopped.

- Determination of disease status: see paragraph 7 (*Response Evaluation*)
- 12-lead ECG
- Documentation of AEs (CTCAE v 4.0 grading)
- Concomitant medications
- ECOG performance status
- Physical examination, including BP measurement
- The following laboratory evaluations will be performed
  - CBC with differential
  - Chemistry and electrolyte panels

- A coagulation panel, including PT-INR and aPTT
- GFR calculation
- AST, ALT, and bilirubin
- Perform drug accountability

### **6.3. Follow-up**

All subjects who finish treatment, whichever the reason, will enter the follow-up. All subjects will be followed until death and data on subsequent treatment will be collected. Follow-up information on tumor status and vital status will be updated every 3 months until death.

### **6.4. Collection of CT scans**

It is required that CT scans or other relevant radiologic examinations used for staging and restaging procedures are collected and made available for eventual revision of response and time-to-progression definition.

**Table 6: Schedule of procedures/assessments**

| Treatment Phase                                                              | Screeninga
(days relative to enrollment) |                |         | Cycle 1
(4 weeks) |       |                |        | Cycle 2
(4 weeks) |       |                |        | Cycle 3 
→ |
|------------------------------------------------------------------------------|---------------------------------------------|----------------|---------|----------------------|-------|----------------|--------|----------------------|-------|----------------|--------|---------------------------|
| Day                                                                          | -28 days                                    | -14 days       | -7 days | Day 1                | Day 8 | Day 15         | Day 22 | Day 1                | Day 8 | Day 15         | Day 22 | Day 1                     |
| ICF signed b                                                      | X                                           |                |         |                      |       |                |        |                      |       |                |        |                           |
| Separate ICF for biologic studies                                            | X                                           |                |         |                      |       |                |        |                      |       |                |        |                           |
| Allocation of Subject ID No.                                                 | X                                           |                |         |                      |       |                |        |                      |       |                |        |                           |
| Demographics                                                                 |                                             | X              |         |                      |       |                |        |                      |       |                |        |                           |
| Medical history                                                              |                                             | X              |         |                      |       |                |        |                      |       |                |        |                           |
| Inclusion/exclusion criteria review                                          |                                             | X              |         |                      |       |                |        |                      |       |                |        |                           |
| Tumor assessment (CT/MRI scan)                                               |                                             | X c |         |                      |       |                |        |                      |       | X d |        |                           |
| 12-lead ECG                                                                  |                                             | X              |         |                      |       |                |        |                      |       | X f |        | X g            |
| PET/TC scan                                                                  |                                             | X              |         |                      |       | X e |        |                      |       |                |        |                           |
| AEs and toxicities h                                              |                                             |                | X       | X-----→              |       |                |        |                      |       |                |        | X→                        |
| Concomitant medications                                                      |                                             |                | X       | X-----→              |       |                |        |                      |       |                |        | X→                        |
| ECOG performance status                                                      |                                             |                | X       | X                    |       |                |        | X                    |       |                |        | X                         |
| Physical examination                                                         |                                             |                | X       | X f       |       |                |        | X                    |       |                |        | X                         |
| CBC with differential i                                           |                                             |                | X       | X f       |       | X              |        | X                    |       | X              |        | X                         |
| Chemistry / electrolyte panel                                                |                                             |                | X       | X f       |       | X              |        | X                    |       | X              |        | X                         |
| Blood for CEC and CEP counts j                                    |                                             |                | X       |                      |       | X              |        | X                    |       |                |        |                           |
| Blood for biomarkers                                                         |                                             |                | X       |                      |       | X              |        | X                    |       |                |        |                           |
| Pregnancy test k                                                  |                                             |                | X       |                      |       |                |        |                      |       |                |        |                           |
| Urinalysis by dipstick (with microscopic analysis if indicated) l |                                             |                | X       | X f       |       | X              |        | X                    |       | X              |        | X                         |
| Proteinuria quantification (if indicated) l                       |                                             |                | X       | X f       |       | X              |        | X                    |       | X              |        | X                         |
| GFR calculation m                                                 |                                             |                | X       | X f       |       |                |        | X                    |       |                |        | X                         |
| Coagulation panel n                                               |                                             |                | X       | X f       |       | X o |        | X                    |       | X n |        | X                         |

|                                        |  |   |   |   |   |   |   |   |   |   |   |
|----------------------------------------|--|---|---|---|---|---|---|---|---|---|---|
| AST, ALT, bilirubin p       |  | X | X | X | X | X | X | X | X | X |   |
| Blood pressure monitoring q |  | X | X | X | X | X | X | X | X |   | X |
| Drug dispensing                        |  |   | X |   |   |   | X |   |   |   | X |
| Drug accountability                    |  |   |   |   |   |   | X |   |   |   | X |

| Treatment Phase                           | End-of-treatment | Safety Follow-up r      | Survival Follow-up s |
|-------------------------------------------|------------------|------------------------------------|---------------------------------|
| Days                                      |                  | 30 ( $\pm$ 7) days after last dose | Q3 months                       |
| CT/MRI scan d                  | X                |                                    |                                 |
| 12-lead ECGg                              | X                |                                    |                                 |
| AEs and toxicities h           | X                | X                                  |                                 |
| Concomitant medications                   | X                | X                                  |                                 |
| ECOG performance status                   | X                |                                    |                                 |
| Physical examination                      | x                |                                    |                                 |
| CBC with differential                     | X                | X                                  |                                 |
| Chemistry / electrolyte panel             | X                | X                                  |                                 |
| Blood for CEC and CEP counts j | X                |                                    |                                 |
| Coagulation panel                         | X                | X                                  |                                 |
| GFR calculation                           | X                |                                    |                                 |
| AST, ALT and bilirubin                    | X                | X                                  |                                 |
| Drug accountability                       | X                |                                    |                                 |
| Survival status                           |                  |                                    | X                               |

AE = adverse event, ALT = alanine aminotransferase, AST = aspartate aminotransferase, CEA = carcinoembryonic antigen, CBC = complete blood count, CRC = colorectal cancer, CT = computed tomography, ECG = electrocardiogram, ECOG = Eastern Cooperative Oncology Group, ID = identification, GFR = glomerular filtration rate, EORTC QLQ-C30 = European Organization for Research and Treatment of Cancer Quality of Life C30 questionnaire, EQ-5D-3L = European Quality of Life Group five dimensions questionnaire 3-level version, ICF = informed consent form, MRI = magnetic resonance imaging, PET = positron emission tomography, PRO = Patient-reported Outcomes.

1 From cycle 3 to the end of treatment, visit on D15 may be scheduled at the discretion of the investigator, if scheduled, visits on D15 should include the same procedures as were performed on D15 C2 (expecting for the plasma biomarker sampling)

- Screening procedures may be completed during multiple visits but must be completed within specified timeframes before the first dose of study drug..
- ICF must be signed before any study-related procedures are performed (including screening procedures); this will include consent for tumor tissue collection (primary tumor

and liver metastases) as well as a separate ICF for molecular analyses of whole blood.

- c. All CT/MRI scans (chest, abdomen, pelvis, and other suspected sites as applicable) to determine eligibility for randomization must be performed with 4 weeks prior to randomization
- d. CT/MRI scans (chest, abdomen, pelvis, and other suspected sites as applicable) will be performed at week 6th and the 12nd week: after CT/MRI scans will be performed at 3-month intervals until disease recurrence as assessed by the investigator.
- e. 18FDG-PET CT scan on day 14 (+/-2) after treatment start (results will not be communicated to the patient and the treating physician)
- f. ECG, physical examination, and laboratory evaluations are not required on Cycle 1, Day 1 if performed within 7 days of initiation of study drug.
- g. After 6 cycles, ECG may be performed at the investigator's discretion. ECG must be performed at End-of treatment.
- h. AE assessment is to be started from signing of ICF until 30 days after the last dose of study drug (Safety Follow-up) and at the discretion of the investigator (serious adverse events only) during Active and Survival Follow-up
- i. Platelet count ( $\geq 100,000$  cells/mm^3), hemoglobin concentration ( $\geq 9$  g/dL), and absolute neutrophil count ( $\geq 1500$  cells/mm^3) without transfusion or granulocyte-colony stimulating factor and other hematopoietic growth factors must be met at study entry
- j. CEC and CEP counts, blood samples to be stored for evaluation of cytokines, circulating angiogenic factors and miRNA plasma levels will be performed on day 14th +/-2 after starting treatment, before starting the 2nd cycle ( day 28) at the first restaging ( after 6 weeks) and at progression of the disease.
- k. Female subjects of childbearing potential must have a negative pregnancy test result  $\leq 7$  days prior to randomization.
- l. A urinalys by dipstick, and a microscopic analysis if the urine dipstick tests shows a change from normal
- m. GFR  $> 30$  mL/min/1.73 m^2 according to the Modified Diet in Renal Disease abbreviated formula
- n. Subjects who are therapeutically treated with an agent such as warfarin or heparin will be allowed to participate if no underlying abnormality in coagulation parameters exists per medical history. If a subject is taking warfarin or heparin with stable PT-INR at baseline, close monitoring of PT-INR and aPTT should be performed  $\geq 1$  times/week until PT-INR and aPTT are stable as compared with a pre-dose measurement (defined by the local standard of care)
- o. Only if subject is maintained on warfarin or heparin
- p. AST, ALT, and bilirubin must be obtained at baseline and monitored weekly during the first 2 cycles of treatment with regorafenib (ie, on Days 1, 8, 15, and 22 of Cycles 1 and 2 [ $\pm 3$  days]), even if values are normal. The investigators may use investigational site or local laboratory AST, ALT, and bilirubin values for subject treatment decisions for Days 8 and 22 of Cycles 1 and 2; these values must be entered in the eCRF.
- q. Blood pressure monitoring required weekly for first 6 weeks
- r. Subjects discontinuing the study for disease recurrence or any other reason will have a Safety Follow-up Visit 30 ( $\pm 7$  days) after the last dose of study drug and enter Survival Follow-up.
- s. Subjects who experience disease recurrence (either during treatment or during Active Follow-up) or otherwise withdraw from the study for any reason other than death will be followed for overall survival unless consent is withdrawn. Such subjects will be evaluated approximately every 3 months to determine their survival status. Survival Follow-up may occur at more frequent intervals at the discretion of the investigator or as per local standard of care. Telephone follow-up is acceptable.

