#### 4. STUDY DESIGN

This is a multicentre, single-arm, phase 2 study according to Simon's two-stage optimal design. This design has been applied to minimize the number of patients exposed to a possibly inactive drug, considering that alternative treatment options exist, although not satisfactory and likely to be more toxic. Patients who will receive at least one dose of study drug will be considered evaluable.

The primary endpoint will be the rate of evaluable patients alive and not progressed at 6 months.

The sample size calculation is based on the following statistical parameters:

- minimum acceptable rate of patients alive without progression at 6 months ( $p_0$ ) = 30%;
- auspicated rate ( $p_1$ ) = 50%
- type I and II errors = 10%.

According to these parameters, 22 evaluable patients should be enrolled at the first stage and the study will proceed to the second stage if at least 8 patients will be alive without progression after 6 months. At the second stage, further 24 evaluable patients will be enrolled for an overall sample of 46 evaluable patients. The study will be considered positive if at least 18 patients out of 46 will be alive without progression at 6 months. It is planned that 5 to 10 centres will participate in the study, which could be completed in 24 months.

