### 9.1 Primary endpoint

The rate of patients alive and not progressed at 6 months is the primary study end-point. This rate will be calculated by dividing the number of evaluable patients alive and not progressed after 6 months from study entry, by the number of enrolled evaluable patients. Exact 95% confidence intervals will be described.

The following will be considered as events:

- progression of disease at any date within 6 months from registration, according to RECIST criteria (including deterioration of clinical conditions that prevent radiological restaging);
- death for any cause within 6 months from registration;
- interruption of regorafenib due to adverse events followed by initiation of an alternative antineoplastic treatment within 6 months from registration.

If drug-related adverse events lead to definitive termination of regorafenib but the clinical condition of the patient does not require immediate switch to a different antineoplastic treatment, the patient can be followed according to protocol schedule and will be defined as success or failure according to the time of disease progression as above.

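### The protocol contradicts itself on tumour assessment after treatment stops without progression, and Section 9.1 leaves the 6-month status of a living, unscanned patient undefined

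*Protocol*

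**What the plan says.** One group of texts ends tumour assessment when treatment ends.

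- **Table 6, post-treatment part.** There are three columns: End-of-treatment, Safety Follow-up and Survival Follow-up. CT/MRI is marked only under the first. The last contains only survival status.
- **Footnote r.** "Subjects discontinuing the study for disease recurrence or any other reason will have a Safety Follow-up Visit", timed from the last dose of drug, and then pass to survival follow-up.
- **Footnote s.** It covers recurrence and withdrawal from the study for any reason but death: "Such subjects will be evaluated approximately every 3 months to determine their survival status". A telephone call is enough.
- **Section 5.3.** A patient who declines further treatment is followed for safety and survival.

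The other group continues tumour assessment until progression.

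- **Footnote d**, on the scans after week 12: "after CT/MRI scans will be performed at 3-month intervals until disease recurrence as assessed by the investigator".
- **Section 7.** CT at weeks 6 and 12 from treatment start and every 3 months after that, with no condition that the patient is still on drug.
- **Section 6.3 Follow-up**, for everyone who finishes treatment for whatever reason: "Follow-up information on tumor status and vital status will be updated every 3 months until death".
- **Section 9.1**, for patients who stop because of drug-related adverse events and need no immediate new therapy: "the patient can be followed according to protocol schedule and will be defined as success or failure", depending on when they progress.

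Footnotes h and s also mention an Active Follow-up. Table 6 has no column for it, and the protocol does not define it.

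Section 9.1 lists three events within 6 months: progression (including clinical deterioration that prevents restaging), death, and an adverse-event stop followed by another antineoplastic treatment. The numerator requires that the patient is alive and has not progressed. The denominator is all evaluable patients.

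**The concern.** The primary endpoint needs progression status at 6 months for every patient who took at least one tablet. Patients who stop early without progression, through toxicity or their own choice, are those for whom the two groups of texts give different instructions. One site can close tumour assessment at the end-of-treatment scan and telephone for survival. Another can go on scanning. Both can point to the protocol.

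Section 9.1 has no class for a patient who is alive at 6 months with no assessment. Section 7.6 does settle this for response rate, where patients with insufficient data count as failures, but the primary endpoint has no parallel sentence.

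The decision rules are counts (8 of 22, then 18 of 46), so a few unclassified patients can decide the result, and someone would have to classify them after seeing the data. Progression-free survival is affected too. Section 9.2 censors at the last visit at which progression was checked, which for these patients would be the end-of-treatment scan. That censoring may be related to prognosis.

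**Working it through.** **1. Inputs.** From Section 4: null rate p0 = 30%, target rate p1 = 50%, type I and II errors 10% each; 22 patients at stage 1, continue if at least 8 succeed; 46 in total, positive if at least 18 succeed. The share m of evaluable patients who are alive but unscanned at 6 months is not in the protocol. I assume 5%, 10% and 15%, or 46 × 0.05 = 2.3 to 46 × 0.15 = 6.9 patients. I also assume that being unscanned is independent of true status. (Section 9.3 gives a different stage 1 rule, of 17 patients. That is a separate matter; the figures here use Section 4.)

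**2. The stated design.** With X1 ~ Bin(22, p) and X2 ~ Bin(24, p),

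P(positive) = Σ over x = 8 to 22 of P(X1 = x) × P(X2 ≥ 18 − x).

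- p = 0.30: type I error 0.0974; probability of stopping at stage 1, P(X1 ≤ 7), 0.671.
- p = 0.50: power 0.9049.

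A search for the smallest expected sample size under p0 returns the same design (8/22, 18/46). The stated design is therefore reproduced.

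**3. Unscanned patients counted as successes.** The apparent rate becomes p + m(1 − p). Under the null this is 0.30 + 0.70m.

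| m | Apparent null rate | Type I error | Stop at stage 1 under the null |
|---|---|---|---|
| 0 | 0.300 | 0.097 | 0.671 |
| 5% | 0.335 | 0.214 | 0.533 |
| 10% | 0.370 | 0.377 | 0.396 |
| 15% | 0.405 | 0.558 | 0.274 |

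Even m = 2%, about one patient in 46, gives 0.137.

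**4. Unscanned patients counted as failures.** The apparent rate becomes p(1 − m).

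| m | Apparent null rate | Type I error | Apparent target rate | Power |
|---|---|---|---|---|
| 0 | 0.300 | 0.097 | 0.500 | 0.905 |
| 5% | 0.285 | 0.064 | 0.475 | 0.845 |
| 10% | 0.270 | 0.040 | 0.450 | 0.762 |
| 15% | 0.255 | 0.023 | 0.425 | 0.656 |

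**5. Which table applies.** The protocol does not say. The event list gives the unscanned patient no event, which points to step 3. The numerator asks for absence of progression, which has not been shown, and that points to step 4.

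**6. Timing of the decisive scan.** Week 12 plus 3 months (about 13 weeks) is about week 25 from treatment start. The endpoint is 6 months (about 26 weeks) from registration. A rule that refers to the 6-month scan therefore needs a window.

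**The case against.** The strongest reply is that the scans are already required. Footnote d belongs to Table 6 and is attached to the CT/MRI row of its post-treatment part. It runs until recurrence, not until end of treatment. The on-treatment part works the same way: its single CT mark is at Cycle 2 Day 15, and week 12 and later scans come only from footnote d. Section 7 and Section 6.3 Follow-up agree with it. Footnotes r and s speak of leaving the study, which is not the same as stopping the drug, and footnote s presupposes a pre-progression Active Follow-up. So a reader might infer that Table 6 puts every such patient on survival-only follow-up, but the documents do not support that. They contradict each other.

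A reader might also infer that unscanned patients count as successes. The event list invites this, but Section 9.1 does not say it, and its numerator equally allows the opposite. The group is also narrower than all early stoppers, because deterioration that prevents restaging and adverse-event stops followed by new therapy are already failures.

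These points limit the claim but do not remove it. Footnote r times its visit from the last dose, so it operates when treatment stops, and Table 6 shows no other route. Section 5.3 concerns stopping treatment, not leaving the study. Section 9.1 makes follow-up permissive, and only for drug-related adverse events. Classifying missing data can be left to an analysis plan, but an analysis plan cannot recover scans that were never taken.

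**Conclusion.** The protocol is internally inconsistent on tumour assessment after stopping without progression, and Section 9.1 does not fix the status of an evaluable patient who is alive with no 6-month assessment. For patients managed under footnotes r and s or Section 5.3, the primary endpoint cannot be determined.

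The direction of error depends on a choice the protocol does not make. Over the assumed 5% to 15%, the error is either a type I error two to nearly six times the designed 0.097, or a power loss of 6 to 25 percentage points. Both ranges rest on the assumed share and on independence between missing scans and true status. They show sensitivity and do not forecast what will happen. The contradiction itself rests on the text alone and needs no assumption.

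**What to change.** 1. Add an Active Follow-up column to Table 6, and define the phase, for patients off treatment without progression. CT/MRI follows the schedule already in Section 7 and footnote d, until progression.
2. Limit survival-only follow-up in footnotes r and s and in Section 5.3 to patients with documented progression or who refuse further assessments.
3. In Section 9.1, make continued follow-up mandatory (will, not can).
4. Add to Section 9.1: *an evaluable patient without a tumour assessment establishing non-progression at the scheduled 6-month scan, within a stated window, counts as not a success.* State the window, since that scan falls near week 25 from treatment start while the endpoint runs from registration.

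**Cost.** An amendment to one table and a few sentences, with no scan beyond those Section 7 already requires. The reported rate may be somewhat lower, and some power is lost if scans are still missed (0.845 if 5% are missed). Continued scanning keeps that share small, and the rule does not let missing scans inflate the type I error.
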